### **Checking Assumptions**

- We will check for the following key assumptions: 1) independence of cases (the study design will satisfy this), 2) normal distribution of random intercepts and slopes as well as residuals, and 3) homogeneity of residual variances across the three treatment groups. To ensure that these assumptions are met, we will visually examine random intercepts, slopes, and residual, using boxplots, and q-q plots, and normalized residuals. If the normality or homogeneity assumption is violated, we will transform the data or use Generalized Mixed Linear Models to incorporate the non-normal distribution of the data. Outliers will be detected using Cook's distance and DFFIT. If one or more outliers are detected, we will check whether there has been a type or data mis-entry.
- The pattern of missingness will be examined in the following order. First, missing observations will be set as a dichotomous variable and its correlation with other factors will be examined. If the missing factor is not significantly related with any other factors, the missingness is tentatively deemed Missing Completely At Random (MCAR), and the Last Observation Carried Forward (LOCF) method will be used for an Intention-To-Treat (ITT) analysis (see below). If the missing factor is significantly related with other factors, the missingness is deemed Missing At Random (MAR), and maximum likelihood estimation will be used to estimate missing observations for the ITT analysis. Second, to test whether the missingness is Missing Not At Random (MNAR) or not, sensitivity analysis will be performed by imputing missing observations using a multivariate multiple imputation method under different scenarios. If the influence of missingness is extensive, multiple-imputed data will be used for the ITT analysis.

### **Detailed Analytic Approach:**

Linear mixed-effects regression (LMER) analyses will serve as the main analytic framework, because it offers distinct advantages in statistical power and estimation of population parameters over ANOVA or MANOVA. First, LMER easily incorporates miscellaneous factors (e.g., blocks and treatment providers) as random effects so that the variances due to those factors can be partitioned. As a result, LMER models typically offer less biased parameter estimation and can also offer higher statistical power. It can model multiple dependent variables (e.g., motor evoked potential amplitude, intracortical facilitation, and short-interval intracortical inhibition for Group 3) and test the effect of treatment for each of these dependent variables simultaneously. This modeling technique avoids alpha inflations which typically result from multiple testing. Finally, LMER's maximum-likelihood estimation allows patients with missing observations to be included in a model if the observations are missing completely at random or missing at random. This advantage is important because some degree of attrition is unavoidable given the longitudinal nature of our project. Because we will stratify our samples by sex, sex will be included in each of the models we will describe below. We will test the significant main effect of sex as well as its interaction with the Treatment factor.

- **Intention to Treat Analysis (ITT):** We will include all randomized study participants who have at least baseline endpoint assessments in our ITT analysis. The ITT analysis is our primary method for assessing outcomes, and how it is performed will be determined based on the pattern of

missingness. If the missingness is deemed MCAR, the LOCF method will be used: simply the most recent valid observation will be "carried forward" to replace the subsequent missing observations. If the missingness is deemed MAR, missing observations will remain as missing, and maximum-likelihood estimation, the default estimation algorithm of LMER, will be used to estimate these observations. If the missingness is found to be MNAR, multiple-imputed data will be used to construct LMER models.

- **Per-Protocol Analysis (PPA):** For the PPA we will exclude study participants who: 1) fail to attend 4 out of 6 treatment sessions; and 2) receive prohibited concomitant interventions (section 5.3.3), or 3) develop an exclusionary medical condition while on study protocol. Finally, we will assess how comparable estimated parameters vary between ITT and PPA analyses. Below we describe our analytic plans for specific outcome measures.

### **Mechanistic Component**

- Group 1 (Muscular Effects):
  - We will test whether three group means will significantly differ from each other at either OA2, OA3, and/or OA4 with the baseline value included in the model as a covariate. Following the significant treatment effect, we will perform Fisher's Least Significant Difference (LSD) to examine which group significantly differs from which without any adjustment. This analytic process will be repeated for the outcomes for the other two Groups.
- Group 2 (Spinal Effects)
  - For short-latency stretch reflex excitability, we will test whether three group means will significantly differ from each other at either OA2, OA3, and/or OA4 with the baseline value included in the model as a covariate.
  - For trunk muscle onset latencies in response to postural perturbations and lumbar motion during volitional movement tasks, EMG responses from eight trunk muscles will be recorded each. To reduce the complexity of the data, we will first perform separate principal component analysis (PCA). The scores of the first principal component (i.e., the linear combination of onset latencies of eight muscles) will then be used as the DV for the LMER analysis. We hypothesize that there are significant effects of treatment on PC scores at OA2, OA3, or OA4, after controlling for the baseline outcome value.
  - For the lumbar motion during volitional movement we will test whether three group means will significantly differ from each other at either OA2, OA3, and/or OA4 with the baseline value included in the model as a covariate.
- Group 3 (Cortical Effects)
  - For motor evoked potential amplitude, intracortical facilitation and short-interval intracortical inhibition, we will test whether three group means will significantly differ from each other at either OA2, OA3, and/or OA4 with the baseline value included in the model as a covariate.
- Exploratory Analyses
 

We will perform three exploratory analyses to examine the relationships between the changes in physiological outcomes and the changes in clinical outcomes as detailed below.

  - We will calculate Pearson product-moment correlation coefficients for parametric data and Spearman's rank correlation coefficients for non-parametric data.

- We will explore the use of multiple regression techniques to elucidate the predictive relationships between and among the physiologic outcomes on clinical outcomes. To determine the relative contribution of the physiologic outcomes, the predictors will be entered simultaneously into the model (or potentially blocked if logical), and we will focus on the  $R^2$  and the semi-partial  $r^2$  values of the individual predictors.
- Lastly, we will conduct a mediational analysis. Here, the clinical outcome data from our primary endpoint (Y) will first be regressed onto the treatment independent variable (X). The baseline clinical outcome ( $Y_{\text{Base}}$ ) will be included as a covariate. The  $X \rightarrow Y$  path represents the *total effect* of the treatment interventions. Next, we will include a mediator in the model: the physiologic outcome immediately following treatment #1 ( $M_1$ ). Additionally, baseline ( $M_{\text{Base}}$ ) data will serve as a covariate. Both direct and indirect effects will be examined to assess the degree of mediation. The same mediational analysis will be repeated using the physiologic outcome obtained 3-days +/-1-day following a course of treatment ( $M_2$ ) as the mediator.

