  - **Methods:** *In this experimental setup, the subject is seated with the lumbar spine in a neutral position. The subject's pelvis is securely fastened using seatbelts that cross the mid-thigh and across the anterior superior iliac spine. A chest harness is snugly attached to the subject at the level of the 3rd thoracic vertebrae. Kevlar cables (3/16" diameter) are attached to load cells affixed to the 4 corners of harness by gimbals and run to the corners of the reference frame through a pulley system to attach to actuators set in force control mode. This will allow us to precisely control the magnitude of the perturbing force as well as the duration of this pulse. Specifically, the participant will sit in the perturbation reference frame with their arms held across their chest. To generate the perturbing force, the actuators will be engaged in pairs (e.g. front, back, left side, right side) to induce a perturbation in one of the following directions: flexion, extension, side-bend left, side-bend right, rotation left, or rotation right. The actuators will provide a 100-ms duration perturbation force equal to 10% of trunk mass calculated from anthropometrics.[52] The forces will be delivered at random time intervals between 2-30 seconds. The onset of the force will result in a small trunk angular displacement (5-10 degrees) and a long latency postural reflex response of the trunk muscles.*
  - **EMG Data:** Surface EMG electrodes will be placed bilaterally over the muscle belly of the following trunk muscles using double sided tape collars: 1) Erector Spinae at the L2 level aligned parallel to the line between the posterior superior iliac spine (PSIS) and the lateral border of the muscle at the 12th rib, 2) Rectus Abdominis (RA) 1 cm above the

umbilicus and 2 cm lateral to the midline, 3) External Oblique (EO) just below the rib cage along a line connecting the most inferior portion of the costal margin and the contralateral pubic tubercle, and 4) Internal Oblique (IO) 1 cm medial to the anterior superior iliac spine (ASIS) and just beneath a line joining both ASIS. EMG signals will be collected using a 16 channel BioPac MP150 System (bandwidth of 10- 500 Hz). The raw EMG data will be amplified (1k), sampled at 5000 Hz, filtered with a 60 Hz notch filter, and then rectified.

- Specifics regarding supplemental research is included in the appendix.

- Lumbar motion during volitional movement tasks

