- Location & Assessment Team: Data will be collected at the Motor Control Laboratory located in Grover Center at Ohio University. Blinded members of The RELIEF Study Team (i.e., blinded students, staff, and the principal investigators) will be involved with the data collection and analysis.
- *Methods: Data will be collected and analyzed as previously described [53-56].* In Brief, participants (while standing) will perform reaching tasks in which they are instructed to touch their index finger to targets located in the mid-sagittal plane. The target locations will be normalized to the subject's hip-to-shoulder length, arm length (humerus + forearm), and hip height. The "high" target will be placed in a position calculated so that the subject (with the elbow extended and the shoulder flexed 90 degrees) could, in theory, reach the target by flexing the pelvis 15 degrees without any flexion of the ankle, knee, and lumbar spine. The "low" target location will be determined such that the subject could, in theory, reach the targets by flexing the hip 60°. Normalization of target location allows for comparison of movement patterns across individuals and is sensitive to changes in low back pain populations.[55, 57-60] The participant will pause at the target for 2 seconds and then return to an upright posture. The participant will be allowed to rest between each trial. After completing the reaches at a comfortable pace, the participant will then be asked to reach for the targets as fast as possible. Again, three fast movement trials at each target location for each hand condition will be collected. Kinematic Data: Movement of light-reflective markers attached to the forearm, humerus, trunk, pelvis, thigh, and shank will be measured and recorded using a Vicon MX-13. The system is an optoelectric-based kinematic system that can track, with a spatial resolution of 0.1 mm, the three-dimensional coordinates of light reflective markers attached to the subject. The time series joint angle data are calculated from the 3-D segment coordinate data using an Euler angle sequence of: 1) flexion-extension, 2) lateral bending, and 3) axial rotation using Motion Monitor software. Kinematic data will be sampled at 100Hz.
- Joint Excursions: Joint excursions are defined as the change in joint angle, and are defined as the difference between the joint angles at the beginning of the trial before the go signal and those extracted 100 ms after target contact

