### 9.1 General Design Issues

#### Mechanistic Component

Below we list our primary and secondary hypotheses for the Mechanistic Component. Note that all sample size calculations are based on the primary hypotheses. For more specific information, see *Data Analysis* below.

- Group 1 (Muscular Effects):
  - Primary Hypothesis
    - We hypothesize that there is a significant effect of treatment on skeletal muscle proton transverse relaxation time (T2) asymmetry of the lumbar muscles either immediately following the first treatment intervention (OA2), post-treatment measure (OA3), and/or follow-up measure (OA4), after controlling for the baseline outcome value.
- Group 2 (Spinal Effects)
  - Primary Hypothesis
    - For short-latency stretch reflex excitability, we hypothesize that there is a significant effect of treatment on this outcome at OA2, OA3, and/or OA4, after controlling for the baseline outcome value.
  - Secondary Hypotheses
    - For trunk muscle onset latencies in response to postural perturbations, we hypothesize that there is a significant effect of treatment on the principal component score (i.e., the linear combination of onset latencies of eight muscles) at OA2, OA3, and/or OA4, after controlling for the baseline outcome value.
    - For lumbar motion during volitional movement tasks, we hypothesize that there is a significant effect of treatment on the principal component score at OA2, OA3, and/or OA4, after controlling for the baseline outcome value.
  - See appendix for hypotheses of the supplemental research
- Group 3 (Cortical Effects)
  - Primary Hypothesis
    - We hypothesize that there is a significant effect of treatment on measures indicative of increased intracortical excitability (i.e., increased motor evoked potential amplitude, increased intracortical facilitation, and/or decreased short-interval intracortical inhibition) at either OA2, OA3, and/or OA4, after controlling for the baseline outcome values.

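### Lumbar motion during volitional movement has two competing dependent variables, kinematic excursion and an EMG onset-latency component, and no rule says which one tests the hypothesis

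*Supplement*

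**What the plan says.** Section 6.2.2, under the lumbar-motion outcome, describes standing reaches to a high and a low target, at a comfortable and a fast pace, with trials for each hand condition. The instrument is optical: "Movement of light-reflective markers attached to the forearm, humerus, trunk, pelvis, thigh, and shank will be measured and recorded using a Vicon MX-13". The variable is kinematic: "Joint excursions are defined as the change in joint angle", taken from before the go signal to shortly after target contact. No EMG outcome is described there. Trunk-muscle EMG appears under the preceding outcome, the seated postural perturbations: "Surface EMG electrodes will be placed bilaterally over the muscle belly of the following trunk muscles using double sided tape collars". Four muscles on two sides make eight channels.

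Section 9.1 lists two secondary hypotheses for Group 2. The one on perturbation latencies concerns "the principal component score (i.e., the linear combination of onset latencies of eight muscles) at OA2, OA3, and/or OA4". The next reads: "For lumbar motion during volitional movement tasks, we hypothesize that there is a significant effect of treatment on the principal component score", and does not say what enters that score.

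Section 9.5, Mechanistic Component, mentions lumbar motion twice under Group 2. The second bullet joins it to the perturbation latencies: "lumbar motion during volitional movement tasks, EMG responses from eight trunk muscles will be recorded each". It plans separate principal component analyses and takes as dependent variable the first component, described as a linear combination of the eight onset latencies. The third bullet says: "For the lumbar motion during volitional movement we will test whether three group means will significantly differ from each other", at the three post-baseline assessments with baseline as covariate, and mentions neither EMG nor a component score.

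**The concern.** Joint excursion says how far a joint moved. An onset-latency component says when muscles switched on. They are different quantities, and a treatment could change one and not the other. The chain of hypotheses in section 1.1 ends with improved volitional movement, and a latency score cannot show that.

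The plan attaches both quantities to the same named outcome and does not say which answers the secondary hypothesis in 9.1. The analyst is left with a choice after the data are seen. The choice carries forward: the exploratory regression and mediation models in 9.5 use the physiologic outcomes as predictors or mediators, so a lumbar-motion mediator would be undefined in the same way.

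**Working it through.** No arithmetic decides this. The plan states no effect size, variance or power for lumbar motion, and 9.1 says that all sample sizes rest on the primary hypotheses. The check sets the statements side by side.

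| Place | Instrument or data | Dependent variable |
|---|---|---|
| 6.2.2, lumbar motion | Marker kinematics during reaching | Joint excursion |
| 6.2.2, perturbations | Surface EMG, 4 muscles x 2 sides = 8 channels | Muscle onset latency |
| 9.1, perturbation hypothesis | Eight muscles | Component of onset latencies |
| 9.1, lumbar-motion hypothesis | Not named | Principal component score, inputs not named |
| 9.5, second Group 2 bullet | EMG from eight muscles, for both outcomes | First component of onset latencies |
| 9.5, third Group 2 bullet | Not named; no EMG or component | Lumbar motion, three-group comparison |

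1. **6.2.2 against the second bullet of 9.5.** The measurement section gives excursion; the analysis bullet gives a component of latencies. These conflict for the same named outcome.

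2. **Second against third bullet of 9.5.** Both name lumbar motion and both adjust for baseline. One uses a component score, the other does not. Nothing orders them.

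3. **9.1 against 9.5.** The onset-latency explanation in 9.1 is attached only to the perturbation hypothesis. The lumbar-motion hypothesis could carry that explanation over, or could mean a component built from kinematic variables. It does not settle the choice. Its reference to a component score does mean that the third bullet of 9.5 fails to match it as written.

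4. **Can both be run?** Possibly. The Experiment 2 checklists in the case report forms instrument participants for EMG and for motion capture before the reaching protocol. EMG during reaching may therefore exist.

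5. **Is the third bullet complete?** No. 6.2.2 defines excursion for joints in general and does not single out the lumbar joint. It has 2 target heights x 2 speeds = 4 task conditions for each hand condition, with repeated trials, and gives no rule for reducing these to one value or modelling them together.

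6. **Status of the outcome.** 9.1 calls it secondary; 9.4 lists it among the primary outcome variables of the mechanistic component. I follow 9.1, because the sample-size statements do.

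**The case against.** The best reply is that the two bullets of 9.5 describe two different outcomes of the reaching task. The second says that EMG is recorded for each task and that the component analyses are separate; the third then deals with the movement itself. Both kinds of instrumentation are on the checklists. On this reading nothing competes: there is a muscle-response outcome and a motion outcome. The reading is possible, but the documents do not state it. 6.2.2 defines no EMG outcome for reaching, the second bullet gives its component score under the name of lumbar motion, and 9.1 has one lumbar-motion hypothesis, stated on a component score.

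Two stronger inferences are tempting and should be resisted. A reader might infer that lumbar motion would be tested only on something that is not motion. The third bullet of 9.5 contradicts that, since it compares the arms on lumbar motion directly. A reader might also infer that 9.1 itself defines lumbar motion by EMG latencies. It does not; that definition comes from 9.5 alone.

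It is also fair to say that the stakes are modest. Group 2 was sized on stretch reflex amplitude at 20 per arm, and that calculation does not use lumbar motion.

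**Conclusion.** The inconsistency stands. Lumbar motion has two candidate dependent variables, one kinematic and one a muscle-timing score, with no rule to choose between them, and 9.1 does not match the direct analysis in 9.5. Either result could be presented as the lumbar-motion finding.

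The size cannot be computed from the documents. A reader might infer a definite loss of power or a definite false-positive rate. A loss of power would need an assumed effect and an assumed correlation between the latency score and excursion, and would not apply to the third bullet, which tests motion directly. As a pure illustration, two independent tests at 0.05, with either accepted, would give 1 - 0.95 x 0.95 = 0.0975. That is a single-time illustration of the incentive, not an error rate for this plan, whose model has three arms, three post-baseline assessments and outcomes of unknown correlation.

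The impact is limited to a secondary mechanistic hypothesis and the exploratory models that reuse the outcome. The stretch-reflex sample size, the other two experiments and the pain and disability co-primaries do not depend on it. It should be corrected, but it does not threaten the main conclusions of the trial.

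**What to change.** Before unblinding:

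- In 9.1 and 9.5, name one kinematic dependent variable for lumbar motion. Either use lumbar joint excursion and state how target height, speed, hand and repeated trials are handled (a named condition, an average, or within-participant factors in the mixed model), or use a principal component analysis whose inputs are excursions. The second option keeps the component score in 9.1; the first needs that hypothesis reworded.
- Limit the EMG onset-latency component to the postural-perturbation outcome, and take lumbar motion out of that bullet of 9.5.
- If EMG recorded during reaching is to be analysed, label it a separate exploratory outcome with its own definition.
- Use the chosen variable wherever lumbar motion enters the exploratory regression and mediation models.

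The cost is a wording change in two sections. The motion-capture data are already part of the protocol, so no new measurement, visit or participant is needed. Because 6.2.3 keeps the investigators and the statistician blinded until the end of the study, the choice can still be made without knowledge of the results by arm.

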### **RCT Component**

To test the following RCT hypotheses, we will collapse the clinical outcome data across the three physiological outcome groups for a total sample size of 54/treatment arm.

- Primary Hypotheses
  - We will use separate analyses to test whether the manipulation or mobilization treatment intervention result in a significantly lower NPR level compared to the Sham Control at the post-treatment measure (OA3, our primary endpoint) after controlling for the baseline value. A 2 point reduction in NPR score will be considered a clinically-meaningful important difference.
  - We will use separate analyses to test whether the manipulation or mobilization treatment intervention result in a significantly lower RMDQ level compared to the Sham Control at the post-treatment measure (OA3, our primary endpoint) after controlling for the baseline value. A 3 point reduction in RMDQ score will be considered a clinically-meaningful important difference.
- Secondary Hypotheses
  - We will use separate analyses to test whether the manipulation or mobilization treatment intervention result in a significantly lower PROMIS-based outcome measures compared to the Sham Control at the post-treatment measure (OA3, our primary endpoint) after controlling for the baseline value.
- Exploratory analysis
  - To examine the immediate and longitudinal effects of the manipulation and mobilization treatment interventions, we will examine whether the treatment groups display significantly lower levels in NPR and/or RMDQ than the Sham Control at the other endpoints (i.e., OA2 and OA4), after controlling for the baseline value as a covariate.
  - We will use separate analyses to test whether the manipulation treatment intervention results in a significantly different NPR or RMDQ level compared to the mobilization treatment intervention at the post-treatment measure (OA3, our primary endpoint) as well as the other endpoints after controlling for the baseline value.

For all analyses two-tailed comparisons will be made with a pre-set significance level of 0.05. For all analyses, if there is a significant main effect, then we will perform Fisher's Least Significant Difference (LSD) to examine which group significantly differs from which without any adjustment. .

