#### RCT Component

To test the following RCT hypotheses, we will collapse the clinical outcome data across the three physiological outcome groups. Our Co-Primary Outcomes are NPR and RMDQ scores. The NPR and RMDQ are classic measures for the assessment of pain and disability in low back pain. Our secondary outcomes are change in PROMIS measures of Pain Behavior, Pain Interference, Pain Intensity, and Physical Function. Our primary endpoint is OA3 (visit 8, 3-days +/-1-day after completion of course of treatment intervention).

- Primary Hypotheses
  - We hypothesize that the Manipulation and the Mobilization groups will display a significantly lower NPR level than the Sham Control at the post-treatment measure (OA3, our primary endpoint) after controlling for the baseline value. Because we have a directional hypothesis, we will use a one-tailed test.
  - We hypothesize that the Manipulation and the Mobilization groups will display a significantly lower RMDQ level than the Sham Control at OA3 after controlling for the baseline value. Because we have a directional hypothesis, we will use a one-tailed test.
- Secondary Hypotheses
  - We hypothesize that the Manipulation and the Mobilization groups will display significantly lower levels in PROMIS Pain Behavior, Interference, Intensity, and/or Physical Function than the Sham Control at OA3 after controlling for the baseline value.

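### Section 9.5 gives two unreconciled decision rules for each co-primary outcome: direct tests against sham, and unadjusted LSD comparisons that follow a significant three-arm main effect

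*Supplement*

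**What the plan says.** Three places in the protocol bear on the decision rule.

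- **Section 9.5, RCT Component, Primary Hypotheses.** "We will use separate analyses to test whether the manipulation or mobilization treatment intervention result in a significantly lower NPR level" compared with sham at OA3, controlling for baseline. The next bullet does the same for disability: "We will use separate analyses to test whether the manipulation or mobilization treatment intervention result in a significantly lower RMDQ level". Neither bullet mentions a preceding three-arm test.
- **Section 9.5, RCT Component, last paragraph.** "For all analyses two-tailed comparisons will be made with a pre-set significance level of 0.05", followed by "For all analyses, if there is a significant main effect, then we will perform Fisher's Least Significant Difference (LSD", the purpose being "to examine which group significantly differs from which without any adjustment". Nothing excludes the co-primary outcomes.
- **Section 9.1, RCT Component.** The hypotheses are directional contrasts with sham: "the Manipulation and the Mobilization groups will display a significantly lower NPR level than the Sham Control". The sidedness is given as "Because we have a directional hypothesis, we will use a one-tailed test".

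The sample size text for the RCT in section 9.2 claims power of 0.80 for a significant treatment effect after unspecified alpha adjustments. It does not say whether the effect meant is the three-arm test or the contrasts with sham.

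**The concern.** On a plain reading, the bullets make each contrast with sham decisive in its own right, while the last paragraph makes pairwise comparisons follow a significant three-arm main effect. The two rules can return different verdicts on the same data. They also differ in type I error and in power, so the choice is part of the design and needs to be settled before the treatment codes are released. If it stays open, a reader of the results cannot tell whether a significant contrast with sham met the trial's own criterion.

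The three-arm test also responds to the difference between manipulation and mobilization, a comparison that section 9.5 lists as exploratory.

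**Working it through.** **Inputs from section 9.2.** 54 per arm, three equal arms, d = 0.5, 10% attrition, so 54 × 0.9 = 48.6, taken as 49 per arm. Alpha 0.05 comes from section 9.5. The SDs are 2.5 (NPR) and 6 (RMDQ). Assumptions not in the documents: no variance reduction from baseline unless stated, and the true mobilization effect where it differs from 0.5.

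**Step 1: the plan's 0.80.** For one contrast, the standardised shift is 0.5 / √(2/48.6) = 2.465.

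- One-sided 0.05: Φ(2.465 − 1.645) = 0.794.
- Two-sided 0.05: Φ(2.465 − 1.960) = 0.693.
- Two-sided 0.05, baseline correlation 0.5 assumed: 2.465 / √0.75 = 2.846, and Φ(2.846 − 1.960) = 0.812.

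The stated power is approximately reproduced by a direct, unadjusted one-sided contrast, or by a two-sided one with a baseline gain. It therefore does not reveal which rule was meant.

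**Step 2: one data set, two verdicts.** Take observed benefits over sham of 0.42 SD (manipulation) and 0.21 SD (mobilization), 49 per arm, 3 × 49 − 3 = 144 degrees of freedom.

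- Direct: t = 0.42 / √(2/49) = 2.08, two-sided p = 0.039.
- Three-arm: F = 49 × (0.21² + 0² + 0.21²) / 2 = 2.16, p = 0.119.

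Manipulation succeeds under the bullets, while under the last paragraph the condition for LSD is not met. In the plan's units, 0.42 SD is 1.05 NPR points (0.42 × 2.5) or 2.52 RMDQ points (0.42 × 6).

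**Step 3: how often.** 200,000 simulated trials per scenario, 49 per arm, pooled variance, two-sided 0.05, with benefit counted as success. Direct means the t-test against sham alone. Gated means the same test counted only if the 2-df F test has p < 0.05. Holm is applied over the two contrasts with sham.

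| True d, manipulation / mobilization | Power, manipulation v sham: direct | gated | Holm | Power of F test | Some sham contrast significant directly, F not |
|---|---|---|---|---|---|
| 0.5 / 0.5 | 0.69 | 0.63 | 0.64 | 0.72 | 11.9% |
| 0.5 / 0.25 | 0.69 | 0.57 | 0.59 | 0.58 | 13.8% |
| 0.5 / 0 | 0.69 | 0.63 | 0.58 | 0.72 | 6.4% |

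The first row is closest to the plan. The RCT text gives one effect size for both therapies, and the mechanistic assumptions put mobilization near manipulation (28, 23 and 18% reductions against 30, 25 and 20%).

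**Step 4: no true effect.** The chance that at least one contrast with sham is significant in either direction, per outcome, is 9.1% direct and 4.2% gated.

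**Step 5: sidedness.** With the one-tailed contrasts of section 9.1 the rules disagree more often: 19.2%, 23.4% and 12.4% in the order of the table. The null rates for apparent benefit are 8.8% direct and 2.4% gated.

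**The case against.** The strongest reply is that there is only one rule. The bullets say what is compared, the last paragraph says how, and separate analyses simply means one model per outcome. Section 9.5 uses the same sequence of main effect then LSD for the mechanistic outcomes, and the revision history (draft dated 25 November 2012) records that LSD was added to the RCT analyses on purpose.

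This shows that the LSD sentence is no stray carry-over, but it does not remove the conflict. The same phrase about separate analyses also introduces the comparison of manipulation with mobilization, where it describes a two-arm test. For the mechanistic outcomes the authors say explicitly that three group means are compared, and the RCT bullets do not. A 2-df F test also cannot deliver the one-tailed contrasts of section 9.1.

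Three stronger readings that a reader might infer are not supported:

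- **That contrasts with sham are forbidden when the main effect is not significant.** The text says what follows a significant main effect. The prohibition is inferred from how protected LSD normally works.
- **That the gate wastes power which an adjusted direct test would recover.** Holm gives 0.58 to 0.64 and the gate 0.57 to 0.63. Most of the gap from 0.69 is the price of controlling error over two contrasts.
- **That Holm is already the plan's method for the RCT.** Section 9.2 lists it under the mechanistic sample size calculation. For the RCT it would be a new choice.

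It also stands that the RCT component is labelled exploratory, and that either rule would be acceptable if clearly named.

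**Conclusion.** The concern holds as a conflict between two decision rules for the same co-primary tests. With 49 per arm and two-sided 0.05, the rules disagree on at least one contrast with sham in about 12% of trials if both therapies have d = 0.5. The range is 6% to 14% if mobilization is assumed to be 0 or 0.25. The null error per outcome over the two contrasts is about 9% direct and 4% gated. These rates rest on the assumed mobilization effect and on no baseline gain. That discordant data sets exist does not depend on either, as step 2 shows.

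This should be fixed, but it does not undermine the trial. The RCT is exploratory and wording alone settles the matter. It still deserves attention, because the component declares co-primary outcomes, a primary endpoint and a power of 0.80.

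**What to change.** Before unblinding, name one decisive rule for NPR and RMDQ. The rule that matches section 9.1 is to fit the three-arm baseline-adjusted model for each outcome and test manipulation v sham and mobilization v sham directly, with Holm or an equivalent adjustment over the two. This would also make concrete the alpha adjustments that section 9.2 leaves unspecified for the RCT.

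Reword only the LSD sentence in the last paragraph of section 9.5, so that it no longer governs the co-primary contrasts but still covers the remaining comparisons. The two-tailed sentence opens with the same words and should not be deleted by accident. Settle one-tailed (9.1) against two-tailed (9.5) testing in the same edit, since the error rates depend on it. Holm over two contrasts works within an outcome and does not by itself say how NPR and RMDQ combine.

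The cost is a change of wording, with no new data or participants. Against unadjusted direct testing, Holm gives up 5 to 11 points of power for manipulation v sham at d = 0.5 (0.69 to between 0.64 and 0.58, before any baseline gain). If the sponsor prefers the gate, the plan should say so in the Primary Hypotheses bullets and withdraw the one-tailed wording.
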